## Abstract

**Introduction:**

Psoriasis vulgaris (PV) is an inflammatory, chronically relapsing dermatological disease associated with significant comorbidities. Ixekizumab is recommended as the first-line therapy for severe PV, but encounters persistent challenges with relapse after treatment discontinuation. In clinical practice, Chinese herbal medicine (CHM) including Guben Qushi Huayu formula (GQHF) has been demonstrated effective in reducing PV relapse. However, there remains a scarcity of high-level evidence-based study in this respect. Therefore, this study aims to preliminarily evaluate the feasibility and acceptability of Ixekizumab combined with GQHF in reducing PV relapse.

**Methods and analysis:**

This study employs a mixed-method research (MMR) design, encompassing both quantitative and qualitative studies. The quantitative study consists of a randomized controlled trial involving 50 participants with severe PV, who will be randomly allocated to the intervention group (Ixekizumab plus GQHF) and the control group (Ixekizumab plus GQHF placebo) in a 1:1 ratio. Relapse rate is the primary endpoint. The qualitative study involves semi-structured interviews to concurrently explore the acceptability of the application of Ixekizumab combined with GQHF among the enrolled participants.

**Discussion:**

This pilot study utilizes MMR to investigate the effect of Ixekizumab combined with GQHF in reducing PV relapse. The findings are expected to provide valuable clinical evidence and a novel therapeutic option for PV. Moreover, it is our intention to conduct a larger MMR trial to further strengthen the clinical evidence and broaden the application of Ixekizumab in combination with GQHF.

**Clinical Trial Registration:**

https://www.chictr.org.cn/index.html, identifier ChiCTR2100054950.

## 1 Introduction

Psoriasis vulgaris (PV) is a chronic immune-mediated relapsing inflammatory dermatological disease (Armstrong and Read, 2020), with an increasing prevalence of approximately 2.0%–4.0% of the worldwide population (Parisi et al., 2020; Armstrong et al., 2021; Mou et al., 2022). Given the aggravation and relapse of PV, it gives rise to multiple comorbidities such as psoriatic arthritis, cardiovascular and cerebrovascular disorders, malignant tumors (Elmets et al., 2019; Griffiths et al., 2021), which led to a substantial economic burden on patients and society (Brezinski et al., 2015; Hamilton et al., 2015). Alarmingly, during the prolonged period of uncontrolled disease, patients with PV are susceptible to psychological disorders such as depression and suicidal tendencies (Egeberg et al., 2019; Bardazzi et al., 2022; Poot, 2017).

Currently, the underlying mechanisms of PV remain incompletely understood. The interleukin-23 and T cell type 17 (IL-23/Th17) pathway is recognized as a potential therapeutic target for PV (Ghoreschi et al., 2021; Sharma et al., 2022), with downstream cytokines such as IL-17 and TNF-ɑ being pivotal in the treatment of PV (Bachelez, 2015; Wcislo-Dziadecka et al., 2016). With the increasing occurrence of severe PV,standard biomedical treatments such as IL-17A inhibitors, TNF-ɑ inhibitors and IL-12/23 inhibitors have been extensively utilized for PV (Dapavo et al., 2022; Bai et al., 2019; Mahil and Smith, 2019). Nowadays, Ixekizumab, as a kind of IL-17A inhibitor, has been applied for severe PV in clinical practice (Tsuda et al., 2016; Craig and Warren, 2020; Gordon et al., 2016). Owing to the rapid onset and notable efficacy, international guideline for PV (Nast et al., 2021) indicates that Ixekizumab is a recommended therapeutic regimen for severe PV. Additionally, several published head-to-head randomized controlled trials have reported that, when compared with IL-12/23 inhibitors and TNF-ɑ inhibitors such as Guselkumab, Ustekinumab and Adalimumab, Ixekizumab showed superior in rapidly relieving psoriatic lesion after 12-week treatment (Blauvelt et al., 2020; Reich et al., 2017; Mease et al., 2020). However, during the treatment discontinuation after relieving psoriatic lesions, Ixekizumab faces challenge of disease relapse, which is the common issue to other biological therapies (Masson et al., 2022; Wang et al., 2020). To date, no clinical consensus and guidelines on reducing and administering PV relapse has been published, which is a gap in the management of severe PV.

Chinese herbal medicine (CHM) has been recommended as an alternative therapy in guidelines (Elmets et al., 2021; Committee on Psoriasis, 2023) and has been utilized for the treatment of PV for centuries (Yang et al., 2023). Relevant studies have indicated that CHM can alleviate psoriatic symptoms and decrease the relapse rate (Chen et al., 2020; Lu et al., 2023; Li et al., 2023; Wang et al., 2024; Huang et al., 2024). Furthermore, when combined with standard biomedical treatment for PV, such as narrow-band UVB, methotrexate, acitretin and cyclosporin, CHM has exhibited superiority in reducing PV relapse (Li et al., 2019; Zhang et al., 2009; Wang et al., 2024). Guben Qushi Huayu Formula (GQHF) is a prescribed CHM that is widely applied for the treatment of PV in clinical practice. Network pharmacology and metabolomics have elucidated the potential action mechanism of GQHF (Xiang, C, 2021). Our team has optimized the efficacy and safety profile of GQHF based on previous clinical studies (Li et al., 2024; Lu, Y et al., 2021; Yu, J et al., 2021). Experimental studies have also reported the therapeutic mechanisms of GQHF in the treatment of PV (Chen, H et al., 2024; Xiang, C, 2021; Chen, W, 2022). Specific to the patients with severe PV, our team has previously conducted two single-arm trials investigating the effect of GQHF combined with IL-17A inhibitors, specifically Ixekizumab and Secukinumab. Within these trials, Ixekizumab and Secukinumab were utilized separately in conjunction with GQHF. The findings indicated that the median time to disease relapse was prolonged when undergoing treatment with Ixekizumab and GQHF, compared to the regimen with Secukizumab and GQHF. Additionally, lower incidence of adverse events was observed in the treatment of Ixekizumab and GQHF.

Aligned with the therapeutic goals for PV (Amatore et al., 2019; Nast et al., 2021; Nast et al., 2020), reducing relapse after remission is a critical objective. Considering the rapid symptomatic relief provided by Ixekizumab and the relapse-reducing properties of GQHF, we aim to conduct a mixed-method research (MMR) study to assess the effect of combining GQHF with Ixekizumab in reducing relapse of PV. We will carry out this study in accordance with the guidelines outlined in the Standard Protocol Project Statement: Recommendations for Interventional Trials (SPIRIT) (Butcher et al., 2022). The findings from this study are expected to provide evidence supporting the combined use of GQHF and Ixekizumab in reducing PV relapse.

## 2 Methods and analysis

### 2.1 Study objective and design

This MMR study aims to preliminarily evaluate the effect of GQHF combined with Ixekizumab in reducing relapse of PV. The MMR study design includes both a quantitative study and a qualitative study. The quantitative study constitutes a randomized, double-blind, placebo-controlled trial to evaluate the feasibility of combined therapy of GQHF and Ixekizumab (Figure 1). The qualitative study is semi-structured individual interviews to explore the acceptability of the combined therapy among the enrolled participants (Figure 2).

**FIGURE 1 F1:**
[figure not shown]
The CONSORT flow diagram of randomized controlled trial. GOHF, Guben Qushi Huayu Formula.

**FIGURE 2 F2:**
[figure not shown]
Flow diagram of study of semi-structured interview.

### 2.2 Quantitative study (A randomized controlled trial)

#### 2.2.1 Study setting

The randomized controlled trial will be conducted at Guangdong Provincial Hospital of Chinese Medicine in Guangzhou, China. All participants will be recruited from public or dermatology outpatient departments.

#### 2.2.2 Inclusion criteria

(1) Patients aged 18–70, with no restriction to gender.(2) Patients diagnosed with severe PV, with psoriasis area severity index (PASI) ≥ 10 or body surface area (BSA) ≥ 10%.(3) Patients with indication of Ixekizumab and without history of inflammatory bowel disease.(4) Patients who have signed the informed consent.

#### 2.2.3 Exclusion criteria

(1) Pregnant or lactating women or those planning pregnancy during the study.(2) Patients with self-rating anxiety scale score >50 or self-rating depression scale standard score >53, or other mental disorders.(3) Patients with basic diseases (such as cardiopulmonary diseases) that cannot be controlled with conventional medication alone; patients with severe infection, (tuberculosis, hepatitis or other infectious history), lymphocyte proliferation, hematopoietic system abnormalities and tumor; patients with severe electrolyte imbalances; patients with immune deficiency and hypersensitivity. Additionally, the following clinical test indicators will result in exclusion: alanine aminotransferase (ALT) or aspartate aminotransferase (AST) levels that are three times the normal value; creatinine levels that are 1.5 times the normal value; a positive serological test for human immunodeficiency virus; any key blood routine indicators lower than the normal range; and patients deemed unsuitable by researchers due to other abnormal laboratory findings.(4) Patients who are allergic to the medication or ingredients used in this study.(5) Patients who have participated in other clinical trials within 4 weeks.(6) Patients who have used CHM, Chinese herbal products or topical therapy (such as antibiotics, external corticosteroids, vitamin D3 analogues, calcineurin inhibitors) within 2 weeks; patients who have used conventional systemic therapies (methotrexate, ciclosporin A, acitretin, fumarates, et al.) or ultraviolet treatment within 4 weeks; patients who have received biomedical treatment within 5 half-life periods (17.5 days of Etanercept, 50 days of Infliximab, 70 days of Adalimumab, 105 days of Ustekinumab, 135 days of Secukinumab, 65 days of Ixekizumab, et al.).(7) Patients who are considered unsuitable for this study by researchers.

#### 2.2.4 Withdrawal criteria

The initial assessment consists of screening based on inclusion and exclusion criteria, informed consent interpretation, and laboratory tests. Indicators for enrolment assessment include PASI, BSA, physicians global assessment (PGA), as well as pruritus scores on the visual analogue scale (VAS). Interpretation of informed consent is performed at the beginning, with explanations provided for any questions arising from participants. In addition, written information and verbal explanation of this study will be provided. Participants are free to withdraw from this study at any time, with or without reasons, and that will belong to the cases of dropout before completing the entire study.

#### 2.2.5 Sample size estimation

This is a pilot study aimed at preliminarily evaluating the effect of GQHF combined with Ixekizumab for PV on relapse reduction. Notably, there is a lack of relevant studies providing basic data for sample size calculation of this study. Additionally, published research (Sim and Lewis, 2012) recommends enrolling at least 50 participants in a dual-arm pilot randomized controlled trial when there is high confidence. Therefore, this study aims to enroll 50 participants for preliminary assessment.

#### 2.2.6 Randomization and blinding

Recruited participants will be randomly allocated to the intervention group and the control group in a 1:1 ratio. Computer-generated random list and permuted block size for center-stratified method are generated with SAS 9.2 software. Participants and researchers will be rigorously blinded to the group allocation. According to the blinding requirement of study, the granule of GQHF and GQHF placebo will be packaged and labeled identically with randomized codes by an independent researcher. The blinding codes are generated after randomization. Blinding will be maintained until data validation and editing are complete, or in the onset of serious adverse events.

#### 2.2.7 Intervention

Ixekizumab, a kind of humanized monoclonal biomedical treatment targeting IL-17A, has been approved for PV by FDA in the United States (Menter et al., 2019) and in China (Chinese Society of Dermatology, 2021). In addition, Ixekizumab is marketed and frequently utilized in clinical practice. Guben Qushi Huayu Formula (GQHF), a kind of CHM, has demonstrated effective for PV in previous clinical and experimental studies (Chen et al., 2024; Zhang et al., 2024; Chen, 2022; Xiang, 2021). The components of GQHF are presented in Table 1.

**TABLE 1 T1:** Component of Guben Qushi Huayu formula.

Scientific name	Pharmaceutical name	Produced from	Doses (g)
*Astragalus membranaceus* (Fisch.) Bge. [Fabaceae]	*Astragali Radix*	Dry rhizoma	30
*Rehmannia glutinosa Libosch*. [Scrophulariaceae]	*Rehmanniae Radix Praeparata*	Dry rhizoma	15
*Atractylodes macrocephala* Koidz. [Asteraceae]	*Atractylodis Macrocephalae Rhizoma*	Dry rhizoma	15
*Smilax glabra* Roxb. [Liliaceae]	*Smilacis Glabrae Rhizoma*	Dry rhizoma	30
*Paeonia lactiflora* Pall. [Ranunculaceae]	*Paeoniae Radix Rubra*	Dry rhizoma	15
*Curcuma phaeocaulis* Val. [Zingiberaceae]	*Curcumae Rhizoma*	Dry rhizoma	10
*Trionyx sinensis* Wiegmann [Trionychidae]	*Trionycis Carapax*	Tergum	30
*Prunus mume* (Sieb.) Sieb. et Zucc. [Rosaceae]	*Mume Fructus*	Fruit	15
*Sarcandra glabra* (Thunb.) Nakai [Chloranthaceae]	*Sarcandrae Planta*	Herbal	15

The intervention group will be administered GQHF granule (Jiangyin, Jiangsu Province, China) after meals twice daily for 12 weeks. Simultaneously, Ixekizumab (Taltz) will be subcutaneously injected with initial dose of 160 mg at week 0 followed by 80 mg fortnightly until week 12. A 36-week follow-up will be carried out subsequently to further observe the clinical effect.

The control group will receive GQHF placebo granule (Jiangyin, Jiangsu Province, China) twice daily for 12 weeks, which is identical with GQHF in appearance and taste. Meanwhile, injection of Ixekizumab (Taltz) will be administered according to the same usage and dosage with the treatment group. The 36-week follow-up period will continue later.

#### 2.2.8 Outcomes

##### 2.2.8.1 Primary outcome

Rate of relapse is the primary outcome, wherein relapse is defined as the loss of response of at least 75% improvement in PASI score from baseline (PASI-75) during the follow-up period by participants who achieve PASI-75 after treatment (Warren et al., 2021; Mrowietz et al., 2015).

##### 2.2.8.2 Secondary outcomes

(1) Time to relapse, defined as the interval between the completion of the last treatment and the occurrence of disease relapse.(2) Improvement in PASI score from baseline.(3) Proportion of participants achieving PASI-75.(4) Proportion of participants achieving at least 90% improvement in PASI score from baseline (PASI-90).(5) Changes in PGA score.(6) Changes in VAS score.(7) Changes in Dermatology Life Quality Index (DLQI) score.(8) Changes in Skindex16 score.

PASI-75, PASI-90, BSA and PGA are the recommended outcome measures for assessing the efficacy of PV (Elmets et al., 2021; Committee on Psoriasis, 2023). Regarding the assessment of quality of life, the DLQI is a validated and recognized measure involving aspects of symptoms, feelings, daily activities, recreation, work, study, personal relationships and therapy (Atwan et al., 2017; Mermin et al., 2016). Additionally, the Skindex 16 is another assessment scale that has been proven sensitive and highly applicable in the treatment of PV (Hopkins et al., 2023; He et al., 2014).

##### 2.2.8.3 Safety evaluation

All adverse events occurring during the study will be recorded, and any serious adverse event will be promptly reported to the Human Research Ethics Committee of Guangdong Provincial Hospital of Chinese Medicine, Guangzhou, China. Laboratory examinations will be conducted periodically, including routine blood tests, liver and kidney function tests, stool test, urine tests, chest radiography and 12-lead electrocardiography.

#### 2.2.9 Timeline of visits

The assessment time points included four periods: enrolment, baseline, treatment, and follow-up. The study procedure is illustrated in Figure 3.

**FIGURE 3 F3:**
[figure not shown]
The schedule of study procedure. PASI, Psoriasis area and severity index; PASI-75, at 75% improvement in PASI score from baseline; PASI-90, at 90% improvement in PASI score from baseline; PGA, Physicians global assessment; BSA, Body surface area; VAS, Pruritus scores on the visual analog scale score; DLQI, Dermatology life quality index.

#### 2.2.10 Data collection and management

Data collection is conducted at each visit, covering the periods of enrolment, baseline, treatment and follow-up. Training on data recording will be provided to all research personnel prior to the commencement of the trial. Data from original documents, such as Case Report Form, will be stored in a password-protected dataset. A double-check will be conducted to ensure the accuracy of recorded data. Any correction to the written text will be documented and dated within the original file. Quality control of the finial data will be held in accordance with relevant national and industry standards.

#### 2.2.11 Statistical analysis

Statistical analyses will be conducted utilizing PASW Statistics 26.0 (IBM SPSS Inc, Armonk, New York, USA) and R statistical software version 4.4.1 by an independent statistician blinded to group allocation. Missing data will be involved with the last observation carried forward (LOCF) method. The primary analysis will be focus on the intention-to-treat (ITT) population, including all randomized subjects. Concerning efficacy analysis, frequency counts and percentages of participants in each arm will be calculated for categorical data (such as relapse rate), and group comparisons will be conducted using chi-squared test or Fishers exact test appropriately. Continuous variables will be presented as means with standard deviations for normally distributed data, or medians with interquartile ranges for non-normally distributed data. Group comparisons will be conducted by the t-test or Wilcoxon rank-sum test. For rank data (such as PGA score), intergroup comparison will be performed using the Wilcoxon rank sum test or Cochran-Mantel-Haenszel test. For repeated measures analysis, generalized estimating equations (GEE) or Cumulative Link Mixed Model (CLMM) will be employed to evaluate data across all follow-up time points. The Log-rank test will be utilized to compare the “time to relapse” and “time to achieve improvement” between two groups. All statistical tests will be conducted using a two-tailed hypothesis, with *p* values ≤0.05 considered indicative of statistical significance.

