## 3 Discussion

The current method capable of rapidly and efficiently eliminating lesions of severe PV is standard biological treatment. Ixekizumab, recognized as an effective biomedical treatment targeting IL-17A, is internationally approved in the treatment of PV (Menter et al., 2019; Chinese Society of Dermatology, 2021) and is recommended as the first-line therapy for severe PV in published guideline (Nast et al., 2021). In addition to rapid lesion remission, Ixekizumab encounters significant challenges in disease relapse following treatment discontinuation. Published researches have demonstrated the median time to relapse for Ixekizumab is approximately 20.4 weeks (Masson et al., 2022; Wang et al., 2020). CHM has been widely applied for the treatment of PV in China, and GQHF as a form of CHM has been used in clinical practice for several decades. Our research team has conducted a variety of clinical and experimental studies to evaluate the efficacy and safety of GQHF (Li et al., 2024; Lu et al., 2021; Chen et al., 2024; Xiang, 2021).

To enhance the clinical application of GQHF for PV, further research is greatly needed, particularly regarding its single use and combined use. Patients with severe PV will be included in this study. This pilot study with MMR design aims to evaluate the effect of GQHF combined with Ixekizumab on relapse reduction in the treatment of PV. MMR, a study design that combines quantitative and qualitative approaches (Moorley and Cathala, 2019; Palinkas et al., 2011), provides comprehensive findings in various perspective, including objective assessment from physicians through quantitative method and individual subjective assessment from patients through qualitative research (Pineda-Canar et al., 2024; Wanqing et al., 2022). Consequently, a randomized, double-blind, placebo-controlled trial as a quantitative and semi-structured interviews as qualitative study will be carried out concurrently to evaluate the feasibility and acceptability of GQHF combined with Ixekizumab in reducing PV relapse.

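### LOCF scores a PASI-75 responder who leaves follow-up before an observed relapse as relapse-free at week 36, so the primary relapse rate is understated

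*Protocol article*

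**What the plan says.** All references are to the protocol article.

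- **Missing data** (2.2.11): "Missing data will be involved with the last observation carried forward (LOCF) method". This is the only missing-data rule given, and no outcome is excluded from it.
- **Primary outcome** (2.2.8.1): "relapse is defined as the loss of response of at least 75% improvement in PASI score from baseline (PASI-75) during the follow-up period", counted "by participants who achieve PASI-75 after treatment".
- **Primary analysis** (2.2.11): "The primary analysis will be focus on the intention-to-treat (ITT) population, including all randomized subjects". Relapse rate is summarised as counts and percentages, and "group comparisons will be conducted using chi-squared test or Fishers exact test appropriately", with a "two-tailed hypothesis, with *p* values ≤0.05 considered indicative of statistical significance".
- **Dropout** (2.2.4): "Participants are free to withdraw from this study at any time, with or without reasons". Such participants are classed as dropouts. No expected dropout rate is given.
- **Expected course after stopping** (Section 3, Discussion): "Published researches have demonstrated the median time to relapse for Ixekizumab is approximately 20.4 weeks". Section 2.2.7 sets 12 weeks of treatment and then 36 weeks of follow-up.

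A log-rank test is planned for time to relapse, but that is a secondary outcome (2.2.8.2).

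**The concern.** LOCF assumes that a participant's state does not change after the last visit. Here the change of state is the endpoint. Active treatment has stopped, the disease is expected to return, and the question is how many relapse within 36 weeks. A responder whose last PASI still meets PASI-75 is frozen as a responder and enters the chi-squared or Fisher table as not relapsed. The earlier such a participant leaves, the more relapse risk is erased.

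Three things are at stake:

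- The relapse rate in each arm is too low.
- If dropout differs between arms, the comparison is distorted.
- Section 3 intends the results as preliminary data for a larger trial, so an understated relapse rate would pass into its planning.

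The secondary scores (PASI, PGA, VAS, DLQI, Skindex-16) are affected in the same way, because values carried forward from a dropout do not reflect later worsening.

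**Working it through.** The plan has no figure to reproduce: the 50 participants come from a pilot-trial minimum (2.2.5), with no relapse or dropout rate behind them. The check below sizes the bias.

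**Inputs from the article.** Median time to relapse m = 20.4 weeks (Section 3); follow-up T = 36 weeks (2.2.7); 50 participants at 1:1, so at most 25 responders per arm (2.2.5, 2.2.6).

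**Assumptions.** Exponential relapse times. A proportion d of responders drops out, at times spread evenly over follow-up and unrelated to relapse. d = 10%, 20%, 30%.

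**Step 1. True relapse by week 36.**
p = 1 − 2^(−36/20.4) = 0.706.

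**Step 2. One participant.** A responder lost at follow-up week 12 while still relapse-free has a chance 1 − 2^(−24/20.4) = 0.558 of relapsing by week 36. LOCF scores this as 0.

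**Step 3. Relapse recorded among dropouts.** With λ = ln 2/20.4, λT = 1.223. Averaged over even dropout times, the chance that relapse was seen before leaving is a = 1 − p/(λT) = 1 − 0.7057/1.2232 = 0.423.

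**Step 4. Rate reported under LOCF.** R(d) = (1 − d)·0.7057 + d·0.4231.

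| Dropout d | True rate | LOCF rate | Understated by |
|---|---|---|---|
| 10% | 70.6% | 67.7% | 2.8 points |
| 20% | 70.6% | 64.9% | 5.7 points |
| 30% | 70.6% | 62.1% | 8.5 points |

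**Step 5. Unequal dropout, no true effect.** 10% against 30%: (0.30 − 0.10) × (0.7057 − 0.4231) = 0.0565, a false difference of about 5.7 points in favour of the arm with more dropout. Swapping the rates reverses the sign.

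**Step 6. Equal dropout, true effect.** Take a hazard ratio of 0.5, so λT = 0.6116, p = 0.4575 and a = 1 − 0.4575/0.6116 = 0.252. The true difference is 70.6 − 45.8 = 24.8 points. At 20% dropout in both arms the second arm's LOCF rate is 0.8·0.4575 + 0.2·0.252 = 0.416, so the reported difference is 64.9 − 41.6 = 23.3 points.

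**Step 7. Sensitivity to dropout timing.** With a constant dropout hazard instead, the LOCF rate at 20% dropout is 64.7% and the false difference at 10% against 30% is 6.2 points. If all dropout came at the start of follow-up, the reported rate would be p(1 − d) and the false difference 0.2 × 0.7057 = 14.1 points.

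**Step 8. Effect on the test.** Exact enumeration of the two-sided Fisher test, 25 responders per arm, no true effect: the false-positive rate is 2.3% without dropout (1.1% in each direction). At the Step 5 rates it is 3.9%, of which 3.5% favours the arm with more dropout and 0.4% the other.

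**The case against.** **Size.** The bias is modest and rests on assumed dropout. A false difference of 5.7 points is 1.4 participants of 25, against a standard error of about 13.5 points, and the Fisher false-positive rate stays below 5%. Nothing in the article supports a 10% against 30% imbalance under a matched placebo. This stands as a limit on size. It does not rescue the rule: the direction of the bias in each arm's rate is known, and it needs no imbalance.

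**Pilot status.** The trial is a pilot. But relapse rate is its primary endpoint, is tested at 0.05, and is meant to inform the next trial.

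**The remedy is imperfect too.** If people leave because they feel worse, censoring is informative. Suppose 20% of responders leave within 4 weeks before relapsing. Simulation then gives Kaplan-Meier 59.1% and LOCF 50.6% against a true 70.6%. At 10% against 30% such dropout, Kaplan-Meier still shows a false difference of about 14 points and LOCF about 20. Kaplan-Meier is better but not sufficient, so the dropouts-as-relapsed analysis must be part of the fix.

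**Stronger readings that a reader might infer, and that the article does not support:**

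- *LOCF always favours the arm with more dropout.* This needs similar relapse risk and dropout timing in the two arms.
- *The granule burden will drive unequal dropout.* Both arms take granules twice daily, the placebo matches in appearance and taste, and granules stop at week 12, before relapse is counted (2.2.7).
- *The secondary scores are frozen near their best.* That describes early follow-up dropouts only. Later ones carry partly worsened values, and those leaving early in treatment carry values near baseline.
- *The planned GEE would be sound on incomplete data as it stands.* Ordinary GEE generally needs data missing completely at random.
- *LOCF also feeds the log-rank test.* The article does not say so.

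**Conclusion.** The concern holds for the primary endpoint. It is a stated choice, not an omission: Section 2.2.11 names LOCF without exception, and with the definition in 2.2.8.1 a responder lost before an observed relapse is counted as relapse-free. The relapse rate is understated in both arms unless none of those dropouts would have relapsed.

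For even dropout of 10% to 30% the shortfall is about 3 to 8.5 points from a true 70.6%. The between-arm effect depends on the dropout pattern: about 5.7 false points at 10% against 30%, none at equal dropout, and in that case a true difference is diluted (24.8 to 23.3 points at 20%). Only the 20.4-week median and the 36-week follow-up come from the article. The exponential curve, the dropout rates and their timing are assumptions, and the figures show scale, not a forecast. The rule should be changed before unblinding.

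**What to change.** 1. **Primary outcome.** Drop LOCF. Estimate the week-36 relapse proportion among PASI-75 responders in each arm by Kaplan-Meier, censored at the last PASI visit, or by multiple imputation of PASI by arm. Report the difference with a 95% confidence interval.
2. **Companion analysis, pre-specified with it.** Count responders who drop out before an observed relapse as relapsed. This leans the other way: in the even-dropout illustration at 20% it gives 64.9% + 0.2 × (1 − 0.423) = 76.5%, above the true 70.6%. Read the two results together.
3. **Repeated measures.** Fit a likelihood-based mixed model, including the planned CLMM, to observed data, or use GEE after multiple imputation. Do not use LOCF-filled data.
4. **Timing.** Record the change before unblinding; Section 2.2.12 puts data lock in November 2025.

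The cost is analysis wording, a little programming and slightly wider intervals. Visits, treatment and sample size do not change, and the planned log-rank test already requires time-to-relapse data.

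### LOCF, stated without exception, counts responders who drop out as relapse-free, so within an arm the primary relapse rate can only be understated

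*Protocol article*

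**What the plan says.** All references are to the protocol article.

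- **Event.** Section 2.2.8.1 makes the rate of relapse the primary outcome. Relapse is "loss of response of at least 75% improvement in PASI score from baseline (PASI-75) during the follow-up period", among participants who reached PASI-75 after treatment.
- **Window.** Section 2.2.7 gives 12 weeks of treatment, then: "A 36-week follow-up will be carried out subsequently to further observe the clinical effect". The window therefore ends 36 weeks after treatment, at about study week 48 (12 + 36).
- **Missing data.** Section 2.2.11 has one rule: "Missing data will be involved with the last observation carried forward (LOCF) method". No endpoint is exempted.
- **Population and test.** The same section says "The primary analysis will be focus on the intention-to-treat (ITT) population, including all randomized subjects". It analyses relapse rate as a count and percentage per arm, by chi-squared or Fisher's exact test.
- **Dropout.** Section 2.2.4 lets participants leave "at any time, with or without reasons, and that will belong to the cases of dropout before completing the entire study". It assigns them no relapse status, and the article gives no expected dropout rate.
- **Time to relapse.** This is a secondary outcome (Section 2.2.8.2), "defined as the interval between the completion of the last treatment and the occurrence of disease relapse", and is compared by a log-rank test (Section 2.2.11).

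**The concern.** Relapse is an event that has to be seen at a visit. When a responder leaves while last seen at PASI-75, carrying that observation forward fills every later visit with a response, so no relapse can ever be recorded for that person. The rule assumes lasting remission after treatment stops, which is the very thing the trial sets out to test. A participant who relapses first and leaves afterwards is still counted correctly, so the error has one direction within an arm.

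Two things are at stake. The first is the absolute relapse rate. Section 3 says the pilot should supply preliminary data for a larger trial, and Section 2.2.5 says basic data for a sample size calculation are lacking, so a low rate would pass into that planning. The second is the comparison, if the arms lose responders at different rates. With at most 25 responders per arm, each would-be relapser who leaves and is carried forward lowers that arm's rate by at least 1/25 = 4 points.

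**Working it through.** The article gives no expected relapse rate or dropout rate, so there is no figure of its own to reproduce. The check sizes the effect of the stated rule.

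**Inputs from the article:** median time to relapse after ixekizumab about 20.4 weeks (Section 3); follow-up T = 36 weeks (Section 2.2.7); 50 participants randomised 1:1, so 25 per arm (Sections 2.2.5 and 2.2.6).

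**Assumptions:** constant relapse hazard; relapse in the quoted median means the same as in Section 2.2.8.1; hazard ratio 0.5 for a GQHF effect; a share s = 10%, 20% or 30% who would leave by 36 weeks.

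**Step 1. True rate.** h = ln 2 / 20.4 per week. Controls: 1 − exp(−36h) = 70.6%. At hazard ratio 0.5: 1 − exp(−18h) = 45.8%. Difference 24.8 points.

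**Step 2. LOCF rate, leaving unrelated to flare.** Leaving hazard g = −ln(1 − s)/36. Only relapses that precede leaving are counted: h/(h + g) × [1 − exp(−36(h + g))], with h/2 in place of h for GQHF.

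| s in both arms | Controls | Shortfall from 70.6% | GQHF, hazard ratio 0.5 | Difference |
|---|---|---|---|---|
| 0 | 70.6% | 0 | 45.8% | 24.8 |
| 10% | 67.7% | 2.9 | 43.7% | 24.0 |
| 20% | 64.7% | 5.9 | 41.5% | 23.2 |
| 30% | 61.5% | 9.1 | 39.2% | 22.3 |

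**Step 3. Unequal leaving, 10% v 30%.**
- No true effect: 67.7 − 61.5 = 6.2 points, in favour of the arm that loses more.
- Hazard ratio 0.5, more controls leave: 61.5 − 43.7 = 17.8 points.
- Hazard ratio 0.5, more leave on GQHF: 67.7 − 39.2 = 28.5 points.

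**Step 4. Flare-driven leaving.** Suppose a share s of would-be relapsers leave just before the loss is seen. In controls LOCF gives (1 − s) × 70.6%: 63.5% at s = 10% and 49.4% at s = 30%. Kaplan-Meier with leavers censored gives 1 − exp(−(1 − s) × 36h): 66.7% and 57.5%. Both are low; LOCF is lower.

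**Step 5. Precision.** Simulation with 25 per arm, leaving unrelated to flare, and exact event times (the visit schedule figure is not shown). The Kaplan-Meier mean in controls is 70.6% at all three shares. For the between-arm difference at hazard ratio 0.5 with equal leaving, root-mean-square error is 13.6 to 14.0 points for LOCF and 13.9 to 15.1 for Kaplan-Meier.

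**The case against.** The strongest case is that the comparison is hardly harmed. With equal leaving unrelated to flare, LOCF trims the difference by at most 2.5 points (24.8 − 22.3) and has a slightly smaller total error than Kaplan-Meier (Step 5). This stands. It limits the firm harm to the absolute rate, and to the comparison when leaving is unequal. With 10% v 30% leaving, Kaplan-Meier has the smaller error when there is no true effect (13.9 v 14.7 points) and when more controls leave (14.5 v 15.4), but not when more leave on GQHF (14.6 v 14.1), although LOCF is then biased upward.

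A reader might infer that LOCF will create a false benefit for GQHF. The article does not support that. It gives no dropout rate in either arm, the trial is double-blind, and the placebo matches in appearance and taste. The 10% v 30% case is a scenario and cuts either way. If the same share of would-be relapsers leaves in each arm because of flare, LOCF shrinks the difference: at hazard ratio 0.5 it is (1 − s) × 24.8, or 22.3 to 17.4 points.

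The 70.6% also rests on more than the article says. Section 3 gives a median only, and does not say that relapse there meant loss of PASI-75. Another curve shape would move the figure up or down. The direction of the error does not depend on it.

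Two further replies carry less weight. The log-rank test can censor dropouts, but it is secondary, and the primary comparison remains a percentage after LOCF. An analysis plan not shown might set another rule for relapse; but the article states a rule and a primary method, so this is a choice fixed badly, not detail left for later.

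**Conclusion.** The point holds. As stated, the rule scores a responder who drops out in response as relapse-free for 36 weeks after treatment, so within an arm it can understate relapse and cannot overstate it. Under a constant hazard from the quoted median, and leaving unrelated to flare, the control rate is 2.9, 5.9 or 9.1 points low at 10%, 20% or 30% leaving. The between-arm difference is little affected if leaving is equal, and is biased towards the arm that loses more if it is not (6.2 points at 10% v 30% with no true effect). The leaving shares and the hazard ratio are assumptions, so the size is uncertain while the direction within an arm is not.

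A reader might also infer that relapse is miscounted in participants who start another psoriasis therapy and stay in follow-up. The article does not show that: their PASI is still observed, LOCF does not touch them, and handling of other therapy may be set out elsewhere.

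**What to change.** Before unblinding, and before the November 2025 data lock in Section 2.2.12, make a short dated amendment:

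1. Exempt the relapse endpoint from LOCF.
2. Among participants at PASI-75 at the end of treatment, censor those who drop out at their last PASI visit in response.
3. Take as the primary estimate the Kaplan-Meier relapse proportion per arm at 36 weeks after the end of treatment, and the difference with its 95% CI. This replaces the LOCF percentage and its chi-squared or Fisher test, and stands beside the log-rank test already planned. State the time origin, because week 36 counted from the first injection would fall only 24 weeks into follow-up (36 − 12).
4. Keep every observed loss of PASI-75 in participants who stay in follow-up as a relapse, whatever other therapy they start.
5. Report dropouts by arm.
6. Add a sensitivity analysis that counts dropout in response as relapse.

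Item 6 should not be the primary count. With leaving unrelated to flare, 1 − exp(−36(h + g)) gives 73.5% v 51.2% at 10% leaving and 79.4% v 62.0% at 30%, differences of 22.3 and 17.4 points, which dilutes the effect more than LOCF does.

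The cost is a little more analysis, with no extra visits and no change to the event definition. Precision falls slightly: the difference has an SD of about 13.9 to 15.1 points, against an LOCF error of 13.6 to 14.0 with equal leaving. Censoring still understates relapse if leaving is flare-driven, though less than LOCF (Step 4).
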